### Qualitative data

Following delivery of all the ACE intervention sessions:The facilitator will be interviewed to explore the training and implementation process and their experiences of delivering ACE including barriers/facilitators to adhering to the ACE protocol.Up to three audiologists from both study sites (up to six in total) will also be interviewed, exploring the capability, capacity and willingness of their audiology departments to support the ACE study within their existing services. The acceptability of study processes will also be explored.A sample of 10–12 participants in the ACE intervention arm and four participants in the control arm (with their SOs if willing) will also be interviewed as soon as possible after the completion of the ACE sessions. We will purposively select participants to ensure a mix of those with good/poor hearing aid outcomes (measured at the fifth and final ACE session and equivalent control arm time point, see figure 1 for outcome measures) as well as ensuring we include some participants who dropped out of the sessions/study, ensuring a wide range of views are collected. Control arm participants will include those who have dropped out from the study where possible, allowing us to explore reasons for this. SOs will be interviewed as part of a dyad with the participant. Semi-structured interviews will explore the acceptability of the ACE (eg, venue, timing, content), its perceived impact (reflecting on hearing aid outcomes) with ACE intervention arm participants; and views on study processes (eg, recruitment, outcome measures and timing) with ACE intervention and control arm participants.

Interviews will be audio-recorded, transcribed verbatim and analysed (with NVivo-11) by the research team led by CJ, using the Framework approach,^63^ which is particularly useful for analysing qualitative data in a pragmatic yet systematic way, where theoretical development is not needed. The steps are familiarisation, construction of a thematic framework, indexing and charting the data, mapping and interpretation.

### Economic analysis and quality of life data

A full cost-effectiveness analysis will not be conducted as this is a feasibility trial, thus the study is not powered to detect significant differences.

The costs of implementing the ACE intervention will be estimated and the potential resource implications versus usual care will be explored. Resource use will be summarised by resource use type (eg, GP appointments, outpatient appointments) and appropriate unit costs to be applied to each resource use type will be identified. These will be sourced from a combination of local costings and national databases.^64^

The costing approach will take a broad analytical perspective accounting for NHS costs and for those observed by patients, although this cost will be presented separately. It is anticipated that additional resources used in the ACE intervention arm will largely be NHS staff time and travel/time for patients and SOs, patients and SOs use of primary and secondary NHS care, any private treatments attended, whether related to their hearing or for any other reason, changes to medication and employment or recreational activities. A draft resource use questionnaire based on these anticipated additional resources was designed for this study. The questionnaire will be developed further and tested during the feasibility trial to ensure that all relevant and necessary data can be collected to establish a reliable and valid tool with which to capture resource use for a future full economic evaluation.

Methods to estimate an incremental cost-effectiveness ratio for the ACE intervention versus treatment-as-usual alone in terms of QALYs will be explored. No health-related quality of life assessment tool is currently sufficiently sensitive to all populations, and in the field of hearing health, there has been limited research to identify the most effective tool. In the UK, NICE advocates the used of the EQ-5D for generating QALYs, although it is acknowledged that this is not always the most sensitive tool for particular populations for whom the majority of its dimensions may not apply.^65^ In the US analysis of a 4-week rehabilitation programme noted above,^47^ the SF-36 was used to generate QALYs rather than the EQ-5D, with the SF-36 showing a reduction in the cost per QALY in favour of the intervention. For the present feasibility trial, both assessments will be used to elicit QALYs and a comparison will be made between the outcomes of the two measures. This will enable a decision to be made as to which tool would be most appropriate in the full-scale trial.

The feasibility work will also be used to help to identify any patterns of missing data and any issues relevant for sensitivity analysis, which will influence statistical plans for dealing with imprecision and other uncertainties in the full RCT. For example, data can be bootstrapped to account for the expected skewness evident in economic cost data. The data collected as part of this feasibility study will be used to inform subsequent pretrial modelling.

### Adverse events

Risks within this study are considered to be minimal. It is considered highly unlikely that the ACE intervention arm will suffer any adverse consequences as a result of receiving the ACE plus treatment-as-usual. Nevertheless, interviews with ACE participants, the ACE facilitator and ACE questionnaire data will be used to monitor this eventuality.

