### Sample size calculation and recruitment

As this is a feasibility study, the main purpose is to assess the acceptability and feasibility of conducting this study, with a view to designing and conducting a future full-scale trial.^54^ Six ACE groups are planned with up to seven patients in each (five minimum). This leads to a maximum sample size of 44 patients and up to 44 SOs for the ACE intervention arm, and 44 in the control arm (n=88). This sample size will allow the SD of the proposed outcome measures to be estimated with reasonable certainty to inform future sample size calculations.^54^ Collectively, the two study sites fit approximately 4300 hearing aids a year and based on their experience we estimate 10% will require extra help at follow-up and be eligible for inclusion. Recruitment of patients commenced on 1 April 2017 and is now underway. The recruitment window is currently planned to end on 28 February 2018 and there is potential to extend this phase until 30 April 2018 if necessary.

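### Every source named for monitoring adverse consequences lies on the ACE side, so no like-for-like ascertainment in the control arm is stated (minor)

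*Protocol article*

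**What the plan says.** The Adverse events section of the protocol article rates risk as minimal and considers one arm: "It is considered highly unlikely that the ACE intervention arm will suffer any adverse consequences". It then fixes the method: "interviews with ACE participants, the ACE facilitator and ACE questionnaire data will be used to monitor this eventuality".

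The Qualitative data section describes the interviews on which this relies. Its lead-in is "Following delivery of all the ACE intervention sessions", and this governs the facilitator interview as well as the others. The participant sample is "A sample of 10–12 participants in the ACE intervention arm and four participants in the control arm", who "will also be interviewed as soon as possible after the completion of the ACE sessions". Selection is purposive, mixing good and poor hearing aid outcomes and "ensuring we include some participants who dropped out of the sessions/study". ACE-arm interviews explore acceptability and perceived impact. The topic shared by both arms is "views on study processes (eg, recruitment, outcome measures and timing) with ACE intervention and control arm participants". Unwanted effects are not among the listed topics.

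Table 1 and the outcome sections list the questionnaires. IOI-HA, SAC, EQ-5D-5L, SF-36 and resource use carry no mark restricting them to the ACE arm, and nor do the significant-other measures IOI-HA-SO and SOS-HEAR. The Statistical analysis section summarises PROMs by arm and reports withdrawals with reasons.

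**The concern.** In an open trial, looking for problems mainly in the arm that receives the intervention makes an isolated report hard to interpret. If an ACE participant mentions distress or strain with a partner, nothing collected in the same way from controls shows how often that arises anyway.

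The study also rehearses data collection for the full RCT, and the acceptability of data collection is among its trial delivery objectives. The success criteria in the Conclusion cover economic, acceptability, outcome and fidelity data, but not harms. A one-sided method could therefore pass into the definitive trial without a two-arm version having been tried.

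This is a matter of what the article states, not of detail that it leaves out. Event definitions, causality rules and reporting routes may well sit in the full protocol and are not at issue here.

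**Working it through.** **1. Named sources against data available**

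| Source | Named for adverse consequences? | Arm | Reach and timing |
|---|---|---|---|
| Participant interviews | Yes | ACE (four control interviews exist but are not named for this) | 10–12, after the sessions |
| Facilitator | Yes | ACE | Delivers all groups; interviewed after the sessions |
| ACE questionnaire data | Yes | Unclear: the ACE arm's forms, or the study's forms | All who return them |
| EQ-5D-5L, SF-36, resource use | Not explicitly | Both | Baseline and 6 months |
| SOS-HEAR (significant others) | Not explicitly | Both | Baseline, week 5 or equivalent, 6 months |
| Withdrawals with reasons | No | Intervention and/or trial | Summarised at the end |

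No instrument in the list is described as asking about unwanted effects.

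**2. Size of the ACE arm**

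The sample size section plans six groups of five to seven patients: 6 × 7 = 42 at most and 6 × 5 = 30 at least. At 1:1 allocation the maximum total is 2 × 42 = 84, which matches the abstract. The 44 per arm and 88 in total printed in the sample size section do not follow from 6 × 7. That discrepancy is a separate matter; I use 42 and show 44 alongside.

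**3. Share interviewed**

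- Of 42: 10/42 = 24% to 12/42 = 29%.
- Of 44: 10/44 = 23% to 12/44 = 27%.
- Of 30: 10/30 = 33% to 12/30 = 40%.
- Controls: 4/42 = 9.5%.

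**4. Illustration only: interviews as the sole source**

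The documents give no event rate, so 2%, 5% and 10% are assumptions. The formula also treats the interviewees as a random sample, which they are not. The chance of at least one affected person among n is 1 − (1 − p)^n:

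| Assumed rate p | n = 10 | n = 12 | n = 42 (all asked) |
|---|---|---|---|
| 2% | 18% | 22% | 57% |
| 5% | 40% | 46% | 88% |
| 10% | 65% | 72% | 99% |

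If nobody reports a problem, the one-sided 95% upper bound is 1 − 0.05^(1/n): 26% for n = 10, 22% for n = 12 and 6.9% for n = 42.

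These are worst-case figures for the plan, because questionnaires and the facilitator reach beyond the interviewees.

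**5. What asking everyone would deliver**

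With 42 per arm and the same rate p in each, the 95% half-width for the difference is 1.96 × √(2p(1 − p)/42). At p = 5% this is 1.96 × √(0.095/42) = 9.3 percentage points. At p = 10% it is 1.96 × √(0.18/42) = 12.8 points. Power for an assumed 5% against 20% is about 55%. The gain is in like-for-like ascertainment, not in a test.

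**The case against.** The case on the other side is substantial, and several stronger readings do not survive it.

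- **A reader might infer that harm cannot be compared with control at all, or that control-arm detection is nil.** The documents do not support this. SOS-HEAR covers relationship changes and emotional reactions, EQ-5D-5L covers anxiety and depression, and SF-36 covers mental health and social functioning. Resource use covers care sought for any reason. All are scheduled in both arms, and PROMs are summarised by arm. Worsening in these areas can be compared descriptively.
- **A reader might infer that a no-harm statement would rest only on the minority interviewed.** It would not. The questionnaires go to every ACE participant, and one facilitator delivers every group. Purposive selection that seeks poor outcomes and dropouts may also find more than a random sample would.
- **A reader might infer that nothing could come to light while groups are running.** Table 1 places participant interviews at ACE week 5, and groups form in separate batches. If interviews follow each group, early ones could precede later groups. Weekly attendance logs and session records exist, week-5 questionnaires would arrive group by group, and the facilitator's first session is supervised. What is true is narrower: each participant's interview comes after that person's own sessions.
- **The label ACE questionnaire data could mean the study's questionnaires**, which go to both arms. The study's own name contains ACE, so that reading is open.
- **The trial is low risk and has no harms objective.**

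All of this reduces the consequence. It does not remove the point: the section considers adverse consequences in the ACE arm only, names no source that is clearly from the control arm, and assigns none of the both-arm data to this task. General health measures are also not the same as asking about unwanted effects.

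**Conclusion.** The point holds as a minor one. The stated method for detecting adverse consequences is one-sided: two of its three sources are plainly ACE-side and the third is ambiguous. Interviews reach 24–29% of a full ACE arm, after the sessions. No like-for-like ascertainment in the control arm is stated, although the data for a rough descriptive comparison of general worsening exist.

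The interview shares rest on an ACE arm of 42 and move little if it is 44. The detection probabilities rest on assumed event rates, random sampling and interviews as the only source, so they illustrate the limits of that source and do not measure the plan as a whole.

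**What to change.** 1. Add one identical question on unwanted or negative effects to the week-5 (or equivalent) and 6-month questionnaires in both arms, for participants and significant others.
2. Amend the Adverse events section to say that questionnaire data from both arms are used for this purpose, which also settles the scope of the third source.
3. Add a line for observed events to the existing weekly session record. It has no control counterpart, so keep it as a supplementary ACE-only source outside the by-arm counts. Keep the interviews as supplementary too.
4. Report the questionnaire counts descriptively by arm to the combined steering and monitoring committee.

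The cost is one item in two existing mailings, one line on an existing form, slight respondent burden and a minor amendment. No visits or staff are added. Recruitment had already begun when the article was written, so participants already past a time point would lack the item; the number asked should be reported with the counts. With about 42 per arm the comparison stays descriptive, but the full RCT would inherit a tested, symmetric method.

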### Trial monitoring and oversight

Due to the low risk nature of this trial, approval has been obtained to set up one independent steering and monitoring committee to undertake the roles traditionally undertaken by the Trial Steering Committee and Data Monitoring and Ethics Committee. Regular meetings of a Study Management Group will take place to oversee the progress of the study and review recruitment. We will establish a Project Advisory Panel (PAP) with between two and four hard of hearing adults or hearing spouses that will meet a minimum of five times over the duration of the project. The PAP is a group of patients, service users, carers and lay members of the public whose role is to support and advise the Study Management Group on all aspects of the study’s progression and management.

### Patient and public involvement

Three patient and public involvement (PPI) activities informed the development of this application. First, a funded public engagement event about public perceptions of hearing impairment was held at the Thackeray Medical Museum in Leeds. This event helped to inform the research question. Participants identified a need for wider availability of treatments additional to hearing aids and that non-technological interventions for hearing-impaired people were a priority. Delegates identified communication education as a useful addition to hearing aid use for many hearing-impaired people and their family members. This feedback informed the study design in the following way: the choice of an interactive communication-based intervention rather than an informational one; the need to ensure that routine practical information about hearing aids and hearing impairment is delivered consistently and checked after fitting.

Second, a focus group was held to consult with service-users on the proposed research question, study design and intervention delivery. Four participants were asked to discuss (a) study information and consent procedures, (b) factors that might encourage or discourage their participation in the proposed study such as the burden of the intervention, (c) types of communication scenarios that are important to them, (d) factors that might motivate them to be more active communicators. The outcomes informed our recruitment strategy to maximise interest, commitment and recruitment rates. The group’s views helped develop study information sheets and operational components of delivering ACE.

Third, the charity Hearing Link, who have extensive experience of PPI and managing and delivering group interventions of this type, were consulted about involving public and patients in operationalising and delivering ACE. Patients and service users and carers are involved in the conduct of this study as active members of the PAP.

We will present the findings of this study in patient forums, Trust bulletins and PPI activities including newsletters and public interest groups who work and support older adults with hearing impairment.

### Data monitoring and management

Information relating to study participants will be kept confidential and managed in accordance with the Data Protection Act, NHS Caldicott Guardian, Research Governance Framework for Health and Social Care and the Research Ethics Committee approval.

Participant details will be stored on a secure password-protected server located at the University of York, for the purposes of assisting in follow-ups during the study. All paper data collected from participants will be maintained in a safe secure environment at York Trials Unit. Paper records will be identified using identifiers rather than personally identifiable information. Analytical datasets will not contain any identifiable information.

The confidentiality of the participants, SOs and audiologists interviewed during their qualitative interviews will be ensured by assigning a unique identification code to electronic sound files and transcripts of interviews, known only to the qualitative researcher and appropriate members of the research team. Any quotes published will be anonymous further protecting participant confidentiality.

## Ethics and dissemination

Since the study started in February 2017, three Health Research Authority (HRA)-approved amendments were added to the protocol and are included in the final version reported here:Revised the fidelity check tool. This was considered a non-substantial amendment.Remove inclusion criteria of <3 hours hearing aid use a day and adjusted inclusion criteria to include moderate benefit. We also gained approval to distribute study information flyers to study site staff and patients. These were considered substantial amendments.Developed a study information flyer to be sent to patients not contactable by telephone for follow-up at the York study site. This was considered a non-substantial amendment.

The proposed study will be conducted in accordance with the MRC Guidelines on Good Clinical Practice in Clinical Trials.

The results from this study will be submitted to the funders, peer-reviewed journals, presented at relevant meetings/conferences and within the participating and other audiology departments. We also intend to present the findings of this study in patient forums, Trust bulletins and PPI activities including newsletters and public interest groups who work and support older adults with hearing impairment.

## Conclusion

This will be the first RCT of this type of group communication programme in the context of a public health service and as an adjunct to hearing aid fitting. The impact of this study will ultimately be realised by a larger fully powered RCT designed to determine the effectiveness of the ACE intervention in improving hearing aid benefit for hearing aid users within the NHS GP referral for a hearing aid pathway in the UK. The outcomes of this study will inform such a RCT.

The feasibility study will be deemed successful if:Seventy per cent of recruitment targets attained for all research components.Study consent/retention rates and proposed sample sizes, indicate delivery of the full RCT is plausible within a 5-year study period.Ninety per cent of ACE groups of five to seven consented participants formed within the intervention window with participants attending three of five sessions.Economic, acceptability, outcome measure and fidelity evaluation data successfully collecteParticipants, SOs and audiologists evaluate acceptability of the ACE and RCT positively.

(Measures with over 10% missing data maybe modified/replaced prior to the main trial).

The criteria for success will result in one of following outcomes:stop: full-scale RCT not be feasible in NHS setting;continue: feasible with modifications;continue: feasible with no modifications, close monitoring;continue feasible as is.
